**6.4.1 Informed Consent**

The parents/legal guardians of the participants must personally sign and date the informed consent form before any study specific procedures are performed. Written and verbal versions of the participant information and Informed consent will be presented to the participants detailing the exact nature of the study; the implications and constraints of the protocol; the known side effects and any risks involved in taking part. It will be clearly stated that the parent/legal guardian is free to withdraw his/her child from the study at any time for any reason without prejudice to future care, and with no obligation to give the reason for withdrawal. Specific consent will be obtained for the genetic analysis to be performed in the study; consent for this may be refused and the participant will still be eligible to participate in the other aspects of the study.

### Parents/legal guardians will be allowed at least 24 hours to consider the information, and the opportunity to question the Investigator, their GP or other independent parties to decide whether they will participate in the study. Written Informed Consent will then be obtained by means of a parent/guardian dated signature and dated signature of the person who presented and obtained the informed consent. The person who obtained the consent would be suitably qualified and trained doctor or research nurse, and has been authorised to do so by the Chief/Principal Investigator. A copy of the signed Informed Consent will be given to the participants. The original signed form will be retained at the study site.

### 6.4.2 Screening and Eligibility Assessment

This is a multi- centre study which is planned to be conducted by the Oxford Vaccine Group, Bristol Children’s Vaccine Centre, Southampton University Hospital, and St George’s Vaccine Institute in the UK and the Malta Children’s Vaccine Group in Malta. An invitation letter, which describes the study and which includes a reply form, would be sent to parents. Parents who are happy to take part are requested to contact the local study team and would then be given the opportunity to discuss the study. An appointment would then be set up for parents willing for their child to take part in the study.

In the UK, eligible participants will be identified through the child health computers of the Primary Care Trusts. Investigators or other allied health professionals at the research sites may also approach parents/carers opportunistically on post-natal wards. Investigators may also ask GPs and Health Visitors within their local network to identify and approach potential parents/carers, who have children of suitable age to participate in the study during the enrolment period. Children of parents interested in participating in the study would then be visited at their homes and recruited to the study after obtaining informed consent.

In Malta eligible participant will be identified through the Birth Register held at Mater Dei Hospital. Children of parents interested in taking part in the study would be given an appointment at the Paediatric Day Care Unit in Mater Dei Hospital and recruited after obtaining informed consent.

Inclusion and exclusion criteria (specified in section 6.3.2 and 6.3.3) will be checked on the first visit during which enrolment and randomisation will take place. Screening procedures are detailed in section 6.4.

The following data will be documented on the CRFs:

Demographics

The date of birth, gender, and ethnicity will be recorded.

Medical History

Details of any history of disease or surgical interventions in all systems will be recorded:

Physical Examination

Axillary temperature will be recorded.

### 6.4.3 Baseline Assessments

Measurement of axillary temperature together with a check of the inclusion and exclusion criteria to determine if the infant is healthy will be performed.

### 6.4.4 Randomisation and Code-breaking

Randomisation for all UK and Maltese participants will take place at the Oxford Vaccine Group in the UK on a 10:10:7:4 basis to the four study groups (Two Dose MenC, Single Dose MenC-CRM197, Single Dose MenC-TT and Control Group). Each study group would then be randomised on a 1:1 basis to the consistent or alternate limb subgroup (a and b). 64 children from each of the Two Dose MenC, Single Dose MenC-CRM197 and Single Dose MenC-TT groups will also be randomly selected, as well as all the children in the Control group, to have the 12 month + 6 day blood visit, . Randomisation will occur by means of opening in a sequential manner a sealed envelope containing the study group the child is to be randomised to. These envelopes will be prepared by the study statistician and the list held by the statistician and the study sites.

Due to the nature of the study, the study is unblinded, therefore no unblinding procedure is required. Analysis of immunogenicity and safety data will be performed by study staff and laboratory staff in linked-anonymised form such that lab samples and diary cards will only be labelled with participant initials/number. In the event of twins being enrolled from the same family, the diary card may be labelled with the participant’s first initial or name.

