**Detailed description of study visits**

**i) Visit 1: Study Day 0: First vaccination visit (6-12 weeks)**

- Written informed consent is obtained from the participant’s parent/guardian.
- Inclusion/exclusion criteria will be checked prior to enrolment.
- A medical and vaccination history will be taken and recorded
- Any concomitant medications which are not listed in the exclusion criteria and thus allowed by the study protocol will be recorded.
- Pre-vaccination assessment of body temperature
- Randomisation
- Vaccination: intramuscular administration of one dose of the vaccines used in the study (according to group) will be administered as described in section 7.
- Explanation of diary cards to assess local and systemic adverse events for 4 days following vaccination

The vaccinees will be observed closely for at least 15 minutes, with appropriate medical treatment readily available in case of a rare anaphylactic reaction following the administration of vaccines.

The subjects’ parents/guardians will be instructed to contact the investigator immediately should they manifest any signs or symptoms they perceive as serious.

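### Section 6.4.4 places the randomisation list at the study sites of an open-label trial and does not bar recruiting staff from it, so the text permits foreknowledge of the next dose group

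*Protocol*

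**What the plan says.** Three statements in Protocol section 6.4.4 bear on concealment.

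- Mechanism: "Randomisation will occur by means of opening in a sequential manner a sealed envelope containing the study group the child is to be randomised to".
- Custody: "These envelopes will be prepared by the study statistician and the list held by the statistician and the study sites".
- Place: "Randomisation for all UK and Maltese participants will take place at the Oxford Vaccine Group in the UK".

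The same section adds: "Due to the nature of the study, the study is unblinded, therefore no unblinding procedure is required".

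On who recruits, section 6.4.2 says: "Investigators or other allied health professionals at the research sites may also approach parents/carers opportunistically on post-natal wards". It also says that the inclusion and exclusion criteria "will be checked on the first visit during which enrolment and randomisation will take place". UK families are seen at home and Maltese families at a hospital day unit. The Visit 1 procedures (section 6.3.6) list consent first, then the eligibility check, and randomisation some steps later, just before vaccination.

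The protocol does not say which role at a site holds the list, who opens the envelope, or whether the list is kept from recruiting staff. It does not define the list.

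**The concern.** Sealed envelopes opened in a fixed order conceal the allocation only if the people who enrol cannot see the sequence. Custody at the sites works against the purpose of the envelopes, and no other provision separates the list from recruitment.

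Blinding after enrolment and concealment before it are separate safeguards. This trial cannot have the former, so it depends more on the latter. A recruiter who knows the next group can approach, encourage, defer or decline a family accordingly, and the groups may then differ before any vaccine is given. Coded laboratory samples limit biased assessment but do nothing about biased entry.

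The comparisons with the Control group are the most plausible place for this. That group gets no infant MenC dose, and section 9.4 itself singles it out as the group whose risk/benefit balance could shift if MenC disease increased.

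**Working it through.** The plan gives no figure on concealment, so this is mainly a reading of the text, with one small calculation.

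**1. Does the list reveal the next allocation?** Section 6.4.4 fixes the opening order as sequential. The custody sentence follows directly and joins the list to the statistician's preparation of the envelopes, so the natural reading is the randomisation list. A list plus a known position gives the next group.

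**2. Does anything restrict access?** I set section 6.4.4 beside sections 6.4.1 and 6.4.2, the Visit 1 procedures, and the sections on monitoring (11), confidentiality (12.4) and data handling (13). None names a custodian at the sites, bars recruiters from the list, or delays access until after enrolment.

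**3. Does the Oxford statement cure it?** Not as written. Section 6.4.2 lists the Oxford Vaccine Group among the recruiting centres, and the list is still said to be at the study sites. The statement also fits poorly with randomisation as a step of a visit held in a UK home or a Maltese hospital, unless allocation is obtained remotely. The protocol does not describe such a procedure.

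**4. Does the Visit 1 order cure it?** Consent before randomisation is correct, and so is the rule "Inclusion/exclusion criteria will be checked prior to enrolment". But order alone does not hide the next group from someone who can see the list. Approach and booking happen before Visit 1.

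**5. Is there room to act on foreknowledge?** Some. Section 6.3.2 asks for a judgement on whether parents are likely to comply and allows entry from 6 to 12 weeks of age. Section 6.3.3 postpones enrolment for acute illness.

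**6. What does the list add to a guess?** Inputs: ratio 10:10:7:4 and N = 498 (sections 6.4.4 and 9.2). The ratio sums to 10 + 10 + 7 + 4 = 31.

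- Plan's group sizes: 498 × 10/31 = 160.6 (stated 160, twice); 498 × 7/31 = 112.5 (stated 114); 498 × 4/31 = 64.3 (stated 64). The ratio is close enough to use.
- Best fixed guess without the list: 10/31 = 0.323, or 32%.
- With the full list and the position in it: 1.

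The 32% assumes that the guesser uses only the ratio and nothing from earlier allocations. The value of 1 applies to a person with access to the list, not to staff in general.

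**7. Is enrolment over?** The Synopsis plans the trial for 2010–2013, and section 6.1 puts participation at 23–24 months. Counting back from the end of December 2013 gives last enrolment at about the end of December 2011 to the end of January 2012. The latest versions in the Amendment History are dated May 2012. Enrolment had probably ended, but the protocol does not say so.

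**The case against.** The strongest reply is that this is a risk in the wording, not a demonstrated failure. The protocol does not say that recruiters see the list, that it is unsealed, or that each site has the whole sequence. The list could even be a log of allocations already made, since sites must know each infant's group for later vaccines and for Visit 6. Families are found largely through registers and letters and have at least 24 hours to decide (sections 6.4.1 and 6.4.2). Participants are healthy term infants, the main endpoint is a laboratory titre, and centre is in the model (section 9.1).

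Much of this stands as a limit on size. It does not remove the point. A log is the less natural reading, and if it was meant the sentence still needs correcting. Adjusting for centre does not undo selection within a centre. No code-break list is needed at the sites of an open-label trial, so the site copy has no stated purpose.

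Stronger readings are tempting, and the document does not support them:

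- *That concealment was lost, with the next group known for all 498 infants.* The text creates an opportunity. It does not say who had access.
- *That the list also reveals limb subgroup and Visit 6 selection.* Both are set by randomisation at enrolment, but section 6.4.4 says only that the envelope contains the study group.
- *That the bias could never be examined because no blood is drawn before Visit 4.* Envelope order and recorded baseline characteristics can still be checked. The lack of an early titre only narrows that check.
- *That the primary result is compromised.* The primary comparison is Single Dose MenC-CRM197 against Two Dose, which excludes Control. The protocol suggests no clear motive for steering between those two groups.

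**Conclusion.** The point holds as a defect in a stated rule of trial conduct: the protocol combines sequential envelopes with a list at the sites and does not separate that list from recruitment. The consequence is exposure to selection bias in the randomised comparisons. It is most plausible for those with Control and weaker for the primary comparison. No size of bias can be derived from the document. The only figure available is the gain in predictability for a person with access, from 32% to certainty.

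This rests on two assumptions: that the list is the randomisation list, and that no document outside the protocol restricts access to it. The separate statement about the Oxford Vaccine Group leaves the place and manner of allocation unreconciled.

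**What to change.** Amend section 6.4.4 to state that:

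1. the randomisation list is held only by the study statistician, or by another person with no part in recruitment;
2. recruiting staff have only opaque, sealed, sequentially numbered envelopes;
3. each envelope is opened only after consent and eligibility are recorded, with its number, date and time logged;
4. sites keep a record of allocations already made, which is all they need for later visits.

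In the same amendment, say where the envelope is opened and by whom, so that this agrees with the statement on the Oxford Vaccine Group. Because that group also recruits, its recruiting staff must be covered by the same restriction.

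If enrolment has already run under the current text, changing the wording will not protect the infants already allocated, and reporting carries the weight. Record and report who had access to the list at each site, audit envelope order against enrolment dates, and present baseline balance by group and site.

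The cost is a few sentences, retrieval of any site copies and some administrative work. Sample size, visits and analysis are unchanged.

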### 6.4.5 Subsequent assessments

A detailed description of subsequent assessments may be found in section 6.3.6.

## 6.5 Definition of End of Trial

The end of trial is the date of completion of all study assays and after administration of any booster doses of vaccines that may be necessary for participants who have sub-optimal results.

## 6.6 Discontinuation/ Withdrawal of Participants from Study Treatment

Each participant has the right to withdraw from the study at any time. In addition, the investigator may discontinue a participant from the study at any time if the investigator considers it necessary for any reason including:

Ineligibility (either arising during the study or retrospective having been overlooked at screening)

Significant protocol deviation

Significant non-compliance with study requirements

An adverse event which requires discontinuation of the study medication or results in inability to continue to comply with study procedures

Consent withdrawal

Lost to follow up

If a participant is withdrawn from the study the blood samples and any safety data already collected would be included in the analysis.

The reason for withdrawal will be recorded in the CRF.

If the participant is withdrawn due to an adverse event, the investigator will arrange for follow-up visits or telephone calls until the adverse event has resolved or stabilised.

## 6.7 Source Data

In this study the CRF will be used as the source document for collection of demographic data, documentation of inclusion and exclusion criteria, medical and vaccination history and the findings on physical examination. If a participant sustains a SAE then hospital records would be accessed after obtaining parental/guardian consent. Identifying information would be stored separately from the CRF.

All documents will be stored safely in locked cupboards during the study and archived for 3 years after the child turns 18 years of age. Access to these documents would only be available to the investigators, monitors and auditors directly involved in the study. On all study-specific documents, other than the signed consent, the participant will be referred to by the study participant number/initials, not by name.

# TREATMENT OF TRIAL PARTICIPANTS

## 7.1 Description of Study Treatment

This is a Phase IV clinical trial and all vaccines used in this study are licensed.

1. **MenC-CRM197: (*Menjugate*, Novartis Vaccines and Diagnositics):** conjugate *Neisseria meningitidis* serogorup C polysaccharide-protein conjugate vaccine33.
2. **MenC-TT: (*NeisVac-C*, Baxter Vaccines):** conjugate *Neisseria meningitidis* serogorup C polysaccharide-protein conjugate vaccine34.
3. **DTaP-IPV-Hib: (*Pediacel*, Sanofi Pasteur, MSD):** combined diphtheria, tetanus, acellular pertussis, inactivated polio, *Haemophilus influenzae* type b (DTPa-IPV-Hib) vaccine35.
4. **PCV13: (*Prevenar-13*, Wyeth Vaccines):** thirteen valent pneumococcal polysaccharide-protein conjugate vaccine36.
5. **Hib-MenC: (*Menitorix*, GlaxoSmithKline Biologicals):** combined *Haemophilus influenzae* type b and *Neisseria meningitidis* serogroup C polysaccharide-protein conjugate vaccine37.

A measles mumps and rubella (MMR) vaccine will be administered during visit 7 but will not form part of the study evaluation.

## 7.1.1 Dosage and administration

Details on the dosage and administration of each vaccine are given in the study flow chart in Appendix A.

The vaccinees will be observed closely for 15 minutes following the administration of vaccines, with appropriate medical treatment readily available in case of a rare anaphylactic reaction.

Vaccination will be performed by a registered doctor or nurse.

**Injection technique**

In order to ensure proper intramuscular injection of the study vaccines, a 23G (0.5mm in diameter) needle of at least 1 inch (2.54 cm) length will be used. All vaccines will be administered intramuscularly. The following injection technique will be used38.

**Injections in the thigh**

The needle is inserted in the anterolateral aspect of the middle third of the thigh in the vastus lateralis muscle at an angle of 90o to the long axis of the leg with the subject supine or whilst held in the ‘cuddle’. If more than 1 injection is to be given in to the thigh then they will be given at least 2.5 cm apart.

**Injections in the deltoid**

The injection in the deltoid will be done using a 25 mm (1 inch), 23 gauge needle. The needle is inserted in the deltoid at 90o to the long axis of the arm.

- 1. **Storage of Study Treatment**

UK

Vaccines are kept in a locked room in each of the study centres. The refrigerator temperature is regularly monitored and any temperature deviation outside the+2oC to +8oC will be communicated to a designated person via a pager system. In the case of refrigerator failure all vaccines will be transferred to a backup vaccine fridge.

Malta

Vaccines are kept locked in a fridge in a locked room at the Paediatric Day Care Unit in Mater Dei Hospital. The refrigerator temperature is regularly monitored and any temperature deviation outside the+2oC to +8oC will be communicated to the chief engineer in hospital via the Building Management System. The chief engineer would then inform a designated study member via a pager system. In the case of refrigerator failure all vaccines will be transferred to a backup vaccine fridge.

## 7.3 Compliance with Study Treatment

Participants are vaccinated during the designated vaccine visits.

## 7.4 Accountability of the Study Treatment

*Menjugate, NeisVac-C, Pediacel, Prevenar-13, Menitorix* and the MMR vaccine will be supplied by Movianto to the each of the UK study sites. The Oxford Vaccine Group would supply all vaccines to the Malta site. All unused vaccines and returned used vials will be retrieved at the end of the study. The vaccines will be collected from the vaccine fridge at the beginning of each day scheduled for study visits. All used vaccine boxes will be returned to OVG at the end of each study day.

## 7.5 Concomitant Medication

Throughout the study the investigators will not prescribe any concomitant medications (with the possible exception of local anaesthetic cream if required for venepuncture). Only healthy infants will be recruited in the study and if the participant receives any of the vaccines/medications included in the exclusion criteria then the participant will not be enrolled but if already enrolled would be included in the ITT analysis but excluded from the according to protocol (ATP) analysis.

The following medications are contraindicated:

1) Concomitant vaccinations, except the study vaccines, rotavirus vaccine, the Hepatitis A and B vaccines, Influenza vaccines, BCG and the Varicella vaccine, that can be administered 14 days before or after study vaccines. (The Varicella vaccine can also be administered 4 weeks before or after other live vaccines, i.e. MMR. Varicella vaccine can also be given in the form of the combined Measles Mumps Rubella Varicella vaccine from 13 months of age).

2) Immunosuppressants e.g. azathioprine, cyclosporine, or prednisolone at a dose of >0.5mg/kg./day or >20mg/day for more than 2 weeks

3) Immunoglobulins and/or any blood product

**8. SAFETY REPORTING**

## 8.1 Definitions

### 8.1.1 Adverse Event (AE)

An AE or adverse experience is:

Any untoward medical occurrence in a patient or clinical investigation participant administered a medicinal product, which does not necessarily have to have a causal relationship with this treatment (the study medication). Since the medicinal products used in this study are vaccines the definition of the specific adverse events of fever and local reactions will follow the Brighton collaboration guidelines39-42.

An AE can be any unfavourable and unintended sign (including an abnormal laboratory finding), symptom or disease temporally associated with the use of the study medication, whether or not considered related to the study medication.

### 8.1.2 Adverse Reaction (AR)

All untoward and unintended responses to a medicinal product related to any dose.

The phrase "responses to a medicinal product" means that a causal relationship between a study medication and an AE is at least a reasonable possibility, i.e., the relationship cannot be ruled out.

All cases judged by either the reporting medically qualified professional or the sponsor as having a reasonable suspected causal relationship to the study medication qualify as adverse reactions.

### 8.1.3 Severe Adverse Events

To ensure no confusion or misunderstanding of the difference between the terms "serious" and "severe", which are not synonymous, the following note of clarification is provided:

The term "severe" is often used to describe the intensity (severity) of a specific event (as in mild, moderate, or severe myocardial infarction); the event itself, however, may be of relatively minor medical significance (such as severe headache). This is not the same as "serious," which is based on patient/event outcome or action criteria usually associated with events that pose a threat to a participant's life or functioning. Seriousness (not severity) serves as a guide for defining regulatory reporting obligations.

